### Potential limitations and risk for bias

The recruitment of potential participants will be via Generali Health Solutions (GHS), who will address insured older persons of “Generali Deutschland Krankenversicherung AG” (Generali Germany Health Insurance AG) and its subsidiary who live in the close area of the participating study centres. They receive detailed study information. The recruitment process could potentially lead to a selective recruitment of those older adults who are intrinsically motivated to exercise and who are already physically active. The fact that our study included older adults with a higher fall risk (according to the Silver Index, > 40%), while still being able to do 30 min of physical activity, could potentially bias our results. This aspect should be kept in mind while interpreting the results of the study. All interested persons had to state that they were willing to be randomised in one of the two groups to minimise dropouts, particularly in the control group. Within the randomisation procedure, a random allocation of all available places for the study is made by drawing lots. The examiners of the centres have no influence on the allocation to the groups, a change between groups is not possible and group preferences are strictly not allowed. Since the therapists do both measurements and the supervision of the training sessions, blinding of assessors is not possible which yields an acceptable risk for bias. The measurements at T_0_, T_1_, T_2_ and T_3_ are standardised and performed in the same room in each study centre by the same assessor. Measurements should be scheduled at the same day of the week and at the same time of the day for the four measurements if possible. The control group does not receive any training treatment, but they obtain the opportunity to use an optimised training programme after the study is finished (including 1-year follow-up). The participants in the control group are instructed to maintain their usual physical activity during the study. Due to the potential bias and influence of different levels of physical activity, the amount is documented through the German PAQ-50 + during the study duration for both groups. With having a multi-centre study, a bias of regional differences should be minimised. Furthermore, health status of older adults can change over the study duration and influence participation, drop-out rate and results of the study. To gain insights here, the EQ-5D-5L is implemented.

This study is expected to lead to new insights which may help establish a new approach to fall prevention training for older adults at risk for falls. Based on the results of the first part of the intervention, adjustments of load criteria, training content, and exercises can be realised for further using of this approach. Together with the SI measurement, the approach includes a systematic and individually tailored innovative fall prevention programme that can be implemented afterwards in a broad fall-prone target group of older adults. The results will be published in a peer-reviewed scientific journal to make them accessible to the scientific community. After the study completion, approaches to examine the cost-effectiveness and develop an implementation plan are relevant aspects for further steps.

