### Study centres

All assessments, the technology-supported exercise programme (TSEP), as well as two sessions in which participants receive instructions for the home-based exercise programme (HBEP) take place in participating study centres in Cologne, Bonn, Dusseldorf, and Bremen, respectively (addresses are included at the end of this protocol). From each centre, 2-4 sport or physio-therapists take part in the research study. Before the start of the intervention, all participating therapists are trained. This training includes several e-learning (online) modules that must be completed before on-site training begins. All training content of this examination is developed by the German Sport University in cooperation with Movendo Technology. The on-site sessions will be implemented by a researcher from the German Sport University together with a Movendo Technology specialist before the study starts to have a high standardisation and fulfil quality criteria for each training and exercising person.

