
### Randomisation procedures

An equal number of participants in the intervention and control group will be determined for each study centre. For this purpose, all eligible participants draw a lot with either INT or CTR after the baseline assessment. The number of lots for INT and CTR is equal and limited. Drawn lots are not returned to the lottery pot until all lots have been drawn. The examiners of the centres have no influence on the allocation to the groups, a change between groups is not possible.

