#### Fall diary

To assess the number of falls, participants are instructed to keep a diary throughout the complete study (i.e., between T_0_ and T_3_). In the context of this study, a fall is defined conform Lamb and colleagues [41] “a fall is an unexpected event in which the participant comes to rest on the ground, floor, or lower level”. In the fall diary, the participant indicates for each day whether one or more of following events [5] occurred; a ‘trip or slip’, a ‘fall without injuries’, or an ‘injurious fall’. In case of a fall, details of the fall are documented in a fall anamnesis questionnaire. After inclusion in the study, participants receive sheets for every month of their study participation. Sheets for completed months are collected every time the participants visit the study centres for assessments.

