### Intervention

#### Technology-supported exercise programme (TSEP)

The first intervention period refers to the technology-supported exercise programme (TSEP) using the hunova robot (Movendo Technology, Genoa, Italy). The hunova robot is a programmable robotic medical device that consists of two electromechanical platforms with two degrees of freedom, one at foot level (foot platform) and one at seat level (seat). Both platforms include two motorized axes. The platforms are rigidly connected to the robot movement axes by means of a torque and force sensor (6-axis sensor). The system allows two degrees of freedom of mobility (forwards-backwards = anterior-posterior and left-right = medio-lateral). The hunova robot can operate in static, active, passive, and assistive modes. Further details can be found in additional file 1. The hunova robot operates in conjunction with a wireless sensor (Inertial Movement Unit - IMU) located on the participant’s torso, to monitor torso motion. All exercises are accompanied by graphical and audio applications (providing biofeedback) run by the remote computer, with which the participant interacts to complete the exercises.

The participants are supervised in a 1:1 situation by a sport or physio-therapist for about 30 min per training session. By performing various functional, balance, and strength exercises on the hunova robot, the participants train within their individual deficit areas of balance and muscle strength while receiving visual feedback via a monitor.

The design of the TSEP training is planned and carried out on three levels. The first level is represented by the training areas, the second level is the type of activity and the third is the difficulty of each activity. The TSEP is the result of the combination of the three layers and the detailed description is provided in the following paragraphs. At first, there is the training layer (level 1), based on the seven subsections of the SI supplemented by a maintenance area, which consists of exercises that train the seven functional areas assessed. These eight training areas are named static balance, dynamic balance, sensory integration, reactive balance, gait speed, limits of stability, sit to stand and maintenance. For each dimension, specific exercises are possible with the hunova robot. A detailed description of all exercises implemented within the TSEP using the hunova robot is presented in Table 1.

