#### Planned statistical evaluation of outcomes

An analysis of primary outcomes (i.e., number of falls and number of persons who have fallen) will be based on binomial regression analyses with demographic variables, physical activity, and health parameters as covariates. Analyses of secondary outcomes (SI and TUG) will be based on 2 × 4 ANOVA / ANCOVA with groups (INT/CTR) and time of assessment (T_0_, T_1_, T_2_ and T_3_) as factors, and will consider demographic variables, physical activity, and health parameters as co-variates. Significant main or interaction effects will be investigated further using Bonferroni post-hoc-tests. The significance level is set to *p* < 0.05.

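### Assessor blinding is ruled out because therapists both test and train, but with 2-4 therapists per centre a participant's tester need not be that participant's trainer

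*Protocol article*

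**What the plan says.** Under Potential limitations and risk for bias, the protocol article gives its reason, "Since the therapists do both measurements and the supervision of the training sessions", and concludes from it that "blinding of assessors is not possible which yields an acceptable risk for bias". The same section says that the four assessments are standardised and "performed in the same room in each study centre by the same assessor", with weekday and time of day held constant where possible.

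Other sections bear on the reason given:

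- Study centres: "From each centre, 2-4 sport or physio-therapists take part in the research study".
- Technology-supported exercise programme: "The participants are supervised in a 1:1 situation by a sport or physio-therapist for about 30 min per training session".
- Randomisation procedures: "all eligible participants draw a lot with either INT or CTR after the baseline assessment".
- Planned statistical evaluation of outcomes: "Analyses of secondary outcomes (SI and TUG) will be based on 2 × 4 ANOVA / ANCOVA".
- Fall diary, the source of the primary outcomes: "To assess the number of falls, participants are instructed to keep a diary throughout the complete study".

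**The concern.** The article presents the lack of assessor blinding as unavoidable. The only ground offered is that one staff group does both jobs. With at least two people in that group at every centre, the ground does not lead to the conclusion.

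TUG, gait speed, the five-times sit-to-stand and the limits-of-stability test all respond to how the task is instructed and how hard the participant is encouraged. An intervention participant may be tested by the therapist who supervised up to 26 of their sessions on site. A control participant has no such relationship with anyone at the centre. The asymmetry lies between the arms and arises after allocation, so neither randomisation nor covariate adjustment removes it. SI and TUG carry the trial's second hypothesis, on fall risk, and the Discussion expects the first positive results on risk factors straight after the robot-supported block. These are therefore measurements on which early conclusions will be drawn.

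**Working it through.** The protocol gives no figure on this point to reproduce. The check is whether the stated impossibility survives comparison with the article's other statements.

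**1. Does any rule tie assessor to trainer?** None was found. The article says that therapists as a group do both tasks. It does not say who assesses whom.

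**2. Can the roles be split with the minimum of two therapists?** Call them A and B. A assesses a participant at T0. If the participant draws the intervention, B trains them; if the control, nobody does. B's assessments mirror this. A's list of participants to test then contains both intervention and control participants, so the rota itself does not tell A the allocation.

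**3. Is the same-assessor rule kept?** Yes. A tests that participant at T0, T1, T2 and T3.

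**4. Does the order of events allow it?** Yes. Lots are drawn after the baseline assessment, so the T0 assessor is fixed before allocation is known and the trainer can be chosen afterwards. T0 is not exposed to allocation; the exposed assessments are T1 to T3.

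**5. Does the workload change?** Inputs: 235 planned participants (sample-size section), four centres, equal arms within centre, 26 supervised sessions per intervention participant (Benefits and risks). Assumptions: centres of equal size and no dropout.

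- Participants per centre: 235 / 4 = 58.75, about 59.
- Intervention participants per centre: 58.75 / 2 = 29.4, about 29.
- Assessments per centre: 58.75 × 4 = 235.
- Supervised sessions per centre: 29.375 × 26 = 763.75, about 764.

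These totals are the same whichever therapist does which task. The calculation shows that no extra assessments or sessions are needed. It does not show that every week's schedule works.

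**6. Which outcomes are exposed?**

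| Outcome | Source in the article | Exposed to tester influence? |
|---|---|---|
| TUG | Mobility test | Yes, timed and effort-dependent |
| SI: gait speed, sit-to-stand, limits of stability | Silver Index, items 1, 8, 7 | Yes, effort-dependent |
| SI: five platform balance tests | Silver Index, items 2-6 | Less so, recorded by the device |
| SI: age | Silver Index | No |
| SI: falls in the last 12 months | Silver Index | Not stated who takes it |
| Falls and fallers (primary) | Participant's diary | Not through the assessor's testing |

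**7. Would a different therapist be blind?** Only in part. Each intervention block lasts 12 to 16 weeks, while control visits are fixed at 16 weeks, so visit timing can reveal the group. The questionnaires about the two programmes at T1 and T2 can apply only to the intervention arm. Staff share the premises, and participants may disclose their group. These routes exist at any staffing level.

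**The case against.** The strongest reply is that the limitation is disclosed, under its own heading, with countermeasures beside it: standardised procedures, same room, same assessor, similar day and time. The article is also silent on who tests whom, and a therapist manual not shown here may contain a rota. Separation of roles would not secure blinding, for the reasons in step 7. Recruitment was still ongoing at publication, so some participants may already have a T0 assessor who trains them, and changing assessor would break the continuity rule. With two therapists, absence cover could force the pairs to cross or delay sessions against the 16-week limit.

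Much of this stands and limits the point. It does not rescue the stated impossibility. Standardisation and continuity do not address a therapist testing their own trainee, and the article does not defer the matter to another document: it gives a conclusion and a reason, and the reason is insufficient.

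A reader might infer three stronger things that the document does not support:

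- **That every secondary outcome is biased.** Several SI inputs are device-recorded, and age cannot be influenced.
- **That the assessor shapes the 12-month fall count in the SI.** The article does not say who takes it. If participants report it, they are unblinded in any case, and a masked assessor would not cure that.
- **That the bias can be put in numbers.** With 235 × 0.70, about 164, completers, an unadjusted two-group comparison has a smallest detectable difference at 80% power of (1.96 + 0.842) × 2 / √164 = 0.438 SD. An assumed shift of 0.1 to 0.2 SD would be 23% to 46% of that (0.1 / 0.438 and 0.2 / 0.438). The shift has no source in the document, and the planned analysis is a 2 × 4 model, so these percentages only restate the assumption.

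**Conclusion.** The point holds for the secondary outcomes. The article's reason does not establish that assessor blinding is impossible, and its description of the residual risk as acceptable has no support in the text. The arrangement permits a trainer to test their own trainee, with a likely bias towards the intervention on TUG and on the gait-speed, sit-to-stand and limits-of-stability parts of the SI. The direction is a judgement resting on the effort-dependence of those tests; the size cannot be derived.

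The number of falls and the number of fallers come from diaries kept by unblinded participants. They are not affected by this point, and the change proposed would not protect them.

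The conclusion rests on two readings: that each centre really has at least two therapists able to do both tasks, and that no unreported constraint ties assessor to trainer. This is a cheap improvement, not a flaw that threatens the primary analysis.

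**What to change.** Replace the statement of impossibility with a rule. For participants not yet allocated, all assessments from T0 to T3 are done by a centre therapist who does not train that participant and is not told the allocation. To support it:

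- Have the lot opened with the training therapist or other staff, not with the assessor.
- Have someone other than the assessor handle the intervention-only questionnaires and the training plans.
- Ask participants not to disclose their group to the assessor.
- Record the assessor's guess of the group at T1, T2 and T3, and report it.

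For participants already enrolled whose T0 assessor also trains them, keep the same assessor and report how many there are. Where a centre cannot separate the roles, state the reason and drop the claim that the risk is acceptable unless it can be supported.

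The cost is rota planning and an entry in the therapist manual; the totals above need no added assessments, sessions or visits. The downsides are scheduling constraints and absence cover in two-therapist centres, and only partial masking at any centre because of visit timing and shared premises. Even partial separation removes the most direct conflict, that of a therapist measuring the results of their own training.

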## Data Availability

Data sharing is not applicable yet to this article as participant recruitment is still ongoing. The datasets generated and/or analysed during the implementation of the study protocol are available from the corresponding author on reasonable request.

## Abbreviations

CTR: Control group
COP: Centre of pressure
COPD: Chronic obstructive pulmonary disease
D: Difficult
E: Easy
FTSST: Five times sit to stand test
GHS: Generali Health Solutions
GSU: German Sport University Cologne
HBEP: Home-based exercise programme
IMU: Inertial movement unit
INT: Intervention group
M: Medium
PAQ: Physical activity questionnaire
PD: Parkinson’s disease
RCT: Randomised controlled trial
SI: Silver Index
TLX: The task load index questionnaire
TSEP: Technology-supported exercise programme
TUG: Timed-up-and-go test
UEQ: User experience questionnaire
USE: Usefulness, satisfaction and ease of use questionnaire
